Primary objective: to compare mean number of adenomas per procedure (MAP) between GGC and SC Key secondary objective: to compare ADR between GGC and SC Other secondary objectives are*: to determine whether there is a difference in MAP and/or ADR between GGC and SC within each of the screening and symptomatic populations to determine whether there is a difference in mean polyps per procedure (MPP) or polyp detection rate (PDR) between GGC and SC to ascertain the nature and distribution of all polyps in the colorectum, including location, size and morphology, comparing GGC and SC to ascertain if there is a difference in the detection rate of sessile serrated polyps (SSP) between GGC and SC to ascertain if there is a difference in cancer detection rate between GGC and SC (this includes polyps removed at colonoscopy and subsequently found to be cancerous, and lesions felt to be cancerous at the time of colonoscopy) to determine whether there is a difference in advanced adenoma detection rate (AADR) between GGC and SC to determine if there is a difference in caecal intubation rate, insertion time to caecum, total procedure time, withdrawal time in the absence of polyps, and colonoscopist‐assessed and nurse‐assessed patient comfort scores between GGC and SC to determine if there is a difference in patient experience between GGC and SC, utilizing a validated patient‐reported experience measure [37] to identify any projected difference in future post‐polypectomy surveillance colonoscopy workload, according to the application of national guidelines [38] to participant‐level polyp data comparing GGC and SC to compare MAP and ADR between BCSP and non‐BCSP colonoscopists, comparing GGC and SC to compare MAP and ADR between colonoscopists of differing experience levels, as indicated by lifetime procedure numbers and average annual numbers of procedures performed in the last 3 years to compare MAP and ADR for the first 20% of study participants scoped by each colonoscopist with the last 20% of participants to identify any changes in MAP or ADR throughout the study to compare baseline MAP and ADR of each colonoscopist (6 months pre‐study) with that colonoscopist's MAP and ADR during the study in the SC arm (to assess for a contamination effect) and for 6 months post‐study (to assess for dependence upon GI Genius™) to collect contemporaneous data on MAP and ADR for colonoscopists not taking part in the study to follow up patients to identify future outcomes related to colorectal polyps or CRC In addition, further secondary objectives are: to collect data that will allow subsequent health economic evaluation to determine the cost effectiveness of GGC compared with SC to undertake a process evaluation including investigation of user experience of GI Genius™ (see Box 3)

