ADR, adenoma detection rate; BCSP, Bowel Cancer Screening Programme; GGC, GI Genius™‐assisted colonoscopy; SC, standard colonoscopy. *secondary objectives 2‐15 will be assessed across the whole study population and between the symptomatic and screening populations.

The primary and key secondary objectives will be assessed across the whole study population, as well as within the symptomatic and screening populations, and according to colonoscopist experience. Other important markers of detection will be measured (such as polyp detection rate and polyp distribution) as well as procedural factors, patient experience and measures of the impact of GI Genius™ on colonoscopy services (especially post‐polypectomy surveillance burden). Given the noteworthy lack of cost effectiveness analysis for most assistive strategies or technologies, data will be collected to enable the economic evaluation of the cost effectiveness of GI Genius™ to inform decisions concerning wider adoption. Additionally, in recognition that financial issues alone do not determine uptake of novel interventions, a process evaluation will be undertaken to appreciate issues potentially affecting adoption and utilization of the GI Genius™ (see Box 3).

BOX 3Description of planned process evaluation**Table jats-table-wrap-3:** 

Evaluating and adopting novel technology, especially high‐cost technology, is often a lengthy and convoluted process, involving multiple stakeholders with often differing and sometimes conflicting priorities. COLO‐DETECT will include a process evaluation [39] which will seek to understand user experience and fidelity in relation to GI Genius™; identify any moderating contextual factors and/or unintended consequences of using GI Genius™; and explore barriers and facilitators to wide‐scale implementation of the technology into clinical practice. This will include scrutiny of trial data (e.g., deviations from protocol) and semi‐structured interviews with a range of stakeholders including (but not limited to) clinician users of the technology, service managers, healthcare commissioners and guideline‐making bodies such as the British Society for Gastroenterology. This will serve as an exemplar for the process of evaluating and adopting novel technology into the National Health Service (NHS).

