### Colonoscopists and training with GI Genius™

Every colonoscopist at participating sites will be eligible to participate. Participating colonoscopists will undergo standardized training in how to use the GI Genius™ and to deliver SC and GGC according to study protocol, after which they will be required to perform a set number of GGC procedures prior to participating. No testing will be conducted unless requested by the colonoscopist. Colonoscopists who perform colonoscopy within the BCSP undergo additional accreditation and so may be considered to represent expert practice [15], meaning that over‐representation of BCSP‐accredited colonoscopists may not reflect routine clinical practice in the UK. A range of experience amongst participating colonoscopists is anticipated and desirable; to facilitate subgroup analysis by colonoscopist experience, it will be assessed by BCSP accreditation status, lifetime procedure numbers and yearly procedure numbers for the last 3 years (Figure 3).

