### Data analysis

A full statistical analysis plan will be developed prior to analysis commencing. Statistical analysis will be performed by NWORTH CTU. The trial statistician and chief investigator will remain blinded throughout the trial and data analysis. The primary outcome, MAP in GGC versus SC, will be analysed using an ANOVA, using the randomization stratification variables as factors. The key secondary outcome, ADR, will be analysed using logistic regression, forcing trial arm into the model and including randomization stratification variables as factors. This approach will also be used to analyse the detection rate of SSPs, advanced adenomas and cancer, as well as caecal intubation rate, and effects on future colonoscopy workload. Subgroup analyses will be conducted on colonoscopist type (i.e., non‐BCSP accredited vs. BCSP accredited) and indication for colonoscopy (screening vs. symptomatic).

Whether group difference (GGC vs. SC) exists for the nature, morphology, and distribution of polyps found in the colorectum, will be analysed using a multinomial logistic regression; polyp size will be analysed using an ANOVA, as will whether group difference (GGC vs. SC) exists for withdrawal times (in procedures where no polyps were found), insertion time to the caecum (or limit of examination where the caecum is not reached), MPP and patient experience (measured using the Newcastle ENDOPREM™).

To identify changes in MAP and ADR over the time of the study (which might occur due to the trial progression effect [46]), detection rates for the first 20% of participants will be compared with those for the last 20% of participants for each colonoscopist, using repeated measures *t* tests and visual plots. Parallel data on reported detection rates amongst a selection of colonoscopists from the same units but not participating in the study will be compared with the measures obtained in the SC group.

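### The check for change in detection over the study is an unadjusted paired t test of first against last 20% per colonoscopist, with no arm named, so it dilutes drift in one arm and mixes drift with case mix

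*Protocol article*

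**What the plan says.** Box 2 of the protocol article (Study objectives) lists as an other secondary objective "to compare MAP and ADR for the first 20% of study participants scoped by each colonoscopist with the last 20% of participants", in order to identify changes in MAP or ADR during the study. The Data analysis section repeats the comparison ("detection rates for the first 20% of participants will be compared with those for the last 20% of participants for each colonoscopist") and fixes the method: "using repeated measures *t* tests and visual plots". The reason given is a possible trial progression effect. Neither place names an arm, an arm-by-time contrast or a covariate.

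Four other provisions bear on this:

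- The footnote to Box 2 says that secondary objectives 2 to 15 "will be assessed across the whole study population and between the symptomatic and screening populations". The first/last-20% comparison is the twelfth in the list, so it is included.
- The next objective in Box 2 compares each colonoscopist's six-month pre-study baseline with that colonoscopist's "MAP and ADR during the study in the SC arm (to assess for a contamination effect").
- Detection rates of non-participating colonoscopists "will be compared with the measures obtained in the SC group" (Data analysis).
- Colonoscopists are trained, "after which they will be required to perform a set number of GGC procedures prior to participating" (Colonoscopists and training with GI Genius™).

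**The concern.** A change in detection during the trial can be at least two different things. Colonoscopists may find more adenomas in the standard colonoscopy (SC) arm as they absorb habits from the device, or their results in the GI Genius-assisted (GGC) arm may change as they get used to it. A difference computed over all of a colonoscopist's participants returns the average of the two drifts, and zero if they are equal and opposite.

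The first and last fifths also contain different patients. The Sample size section treats screening and symptomatic patients as different: it sets clinically meaningful differences of 10% and 5% in ADR and 0.50 and 0.30 in MAP, and it aggregates BCSP and non-BCSP baselines. The main MAP and ADR analyses include the stratification factors, but this check does not. If the referral mix moves during recruitment, the crude rate moves with it.

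At stake is the interpretation of a supportive analysis. A null result may be taken as reassurance that it cannot give, and a positive result may reflect who was recruited.

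**Working it through.** **The plan's own figure.** No sample size or power is given for this check, so I anchor on the trial's. For ADR 27.6% against 34.6% (difference 7 points = 0.4 × 10 + 0.6 × 5), two-sided 5%, 90% power, unpooled variance: n per arm = (0.276 × 0.724 + 0.346 × 0.654) × (1.960 + 1.282)² / 0.07² → 914, so 1828 in total, and 1828 / 0.9 → 2032. The stated numbers reproduce.

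**Best-case precision of the planned contrast.** Each window holds 0.2 × 2032 ≈ 406 participants. With both arms together, ADR is (27.6 + 34.6) / 2 = 31.1%. With equal volumes, the SD of last minus first is √(2 × 0.311 × 0.689 / 406) ≈ 3.2 points, so the 95% CI is at least ±6.4 points, close to the trial's whole 7-point target. Uneven volumes widen it, because the t test weights every colonoscopist equally. Simulated SDs ran from 3.3 to 5.3 points.

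**Dilution by arm.** Allocation is 1:1, so an SC-only change of 7 points appears as 0.5 × 7 = 3.5 points, and +7 with −7 appears as 0. If the drift is linear over each colonoscopist's series, the windows centre on 10% and 90% of it and see only 0.8 of the drift. Then 7 points in SC becomes 5.6 in SC and 2.8 with both arms together.

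**Detecting a linear 7-point SC-only drift** (normal approximation, two-sided 5%):

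| Analysis | Signal | SD | Power |
|---|---|---|---|
| Planned, arms together, equal volumes | 2.8 | 3.2 | 14% |
| Planned, arms together, uneven volumes | 2.8 | 3.7 to 5.3 | 12% to 8% |
| First/last 20%, SC only, equal volumes | 5.6 | √(2 × 0.276 × 0.724 / 203) = 4.4 | 24% |
| Slope over all 1016 SC participants | 7 | √(12 × 0.276 × 0.724 / 1016) = 4.9 | 30% |
| The same, adjusted for referral category | 7 | 4.6 | 33% |

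The last row takes the variance explained by referral (0.4 × 0.6 × 0.29² = 0.020) from 0.200. Simulations with 2032 participants, 40 or 80 colonoscopists, screening and symptomatic ADR of 45% and 16%, and linear drift agree: about 10% for the planned test and 31 to 36% for the model. For opposite 7-point drifts they give 4 to 5%, against 55 to 64% for the arm-by-sequence term. If the change is a full 7-point step between the windows, the planned test detects it in 17 to 19% of trials, against 24 to 31% in SC alone.

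**Case mix with no true change.** Crude shift = change in screening share × (screening ADR − symptomatic ADR). The document gives neither ADR, only the constraint 0.4 × screening + 0.6 × symptomatic = 27.6%. For a share moving from 30% to 50%:

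| Assumed screening ADR | Implied symptomatic ADR | Crude shift |
|---|---|---|
| 35% | 22.7% | 2.5 points |
| 40% | 19.3% | 4.1 points |
| 45% | 16.0% | 5.8 points |
| 50% | 12.7% | 7.5 points |

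At 45%, with a linear change in share, the whole-population test was significant in 15 to 31% of simulated trials with no true change, against 5 to 6% for an adjusted model. A full 20-point step between the windows raises this to 46 to 48%. The same t test run within each population was significant in 4 to 6%, which is nominal.

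**Window size.** With 30, 50 or 100 colonoscopists, each window averages about 14, 8 or 4 participants per colonoscopist. At 40% screening, the population split leaves about 5, 3 or 2 screening patients.

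**The case against.** The defence has substance, and several parts of it stand.

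- **Pooling of arms is inferred.** The article never says that the arms are combined, and a statistical analysis plan could split them. This stands as a limit on certainty. It is still the natural reading, because the neighbouring checks name the SC arm or group and this one does not. The t test itself is stated, not left open.
- **Case mix is partly handled.** The Box 2 footnote repeats this objective by population, and within one population a change in screening share cannot move the rate. A reader might infer that nothing guards against a referral shift, and the footnote contradicts that. The whole-population test remains exposed, and the split neither separates the arms nor deals with age and sex.
- **Contamination has its own checks.** A reader might infer that the stability of the SC comparator rests on this analysis alone. It does not: baseline against in-study SC, and non-participants against SC, are both planned, and the GGC run-in limits early learning. As described, however, neither comparison gives a time course within the trial.
- **Equal weighting is a legitimate target.** Mean change per colonoscopist is a valid quantity, and first-against-last is a recognised simple contrast. Equal weighting is therefore a cost in precision, not an error. Nor can one say that colonoscopists with fewer than five participants drop out, since no rounding rule is given.
- **The model is not powerful either.** At about 30 to 35% it would miss a 7-point SC drift roughly two times in three. This is correct and limits what the fix can promise.

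**Conclusion.** The point holds as a weakness in a stated method for a supportive secondary analysis. Read as written, the test halves a drift in one arm, cannot see opposite drifts, leaves 60% of participants unused, and in its whole-population form can report a recruitment shift as a change in detection. Its best-case 95% CI of about ±6.4 ADR points means that a null result reassures little.

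The halving and cancelling follow from 1:1 allocation once the arms are taken together. The detection rates and the case-mix false-alarm rates rest on assumed numbers of colonoscopists, volume spread, population-specific ADRs and shape of drift, none of which the document gives. They show direction and rough size only.

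A reader might go further and doubt the trial's main results. The document does not support that: MAP and ADR are compared between concurrently randomized arms with the stratification factors included, and no decision depends on this check. It should be changed because the change is cheap, not because the trial's conclusions hang on it.

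**What to change.** Make the formal test a regression on all participants: logistic for ADR, and the primary-outcome model for MAP. Include a colonoscopist effect, the participant's position in that colonoscopist's series (scaled 0 to 1), arm, arm-by-position and the stratification factors, including referral category. Report the SC slope, the GGC slope and their difference, each with a 95% CI. Use standard errors clustered on colonoscopist, or a random slope, so that colonoscopists may still differ in how much they change, as the paired t test allows. Keep the first/last-20% comparison and the plots as a descriptive display by arm, and keep the planned repeat by population.

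The cost is wording in the analysis plan and a little more analysis work. Colonoscopist ID, arm and indication are already on the CRF, order follows from procedure dates, and coded arm labels preserve the statistician's blinding. The downside is a modelled trend in place of a simple contrast. Precision also stays modest: the SC slope has a 95% CI of about ±9 points (1.96 × 4.6), so a null result should be read through its interval.

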Upon attending for colonoscopy, consent will be confirmed in writing and participants will complete the EQ‐5D‐5L health‐related quality of life questionnaire [40]. Participants will be randomized by recruiting staff 1:1 to GGC or SC [41] using a secure web‐based platform. Randomization will be stratified by age category (<60 years, between 60 and <74 years, ≥74 years), sex, study site and referral category (symptomatic or screening population). In the event of randomization platform unavailability, a coin toss will be used.

Standard colonoscopy represents standard care for colonoscopy at each study site. GGC incorporates all elements of SC and differs only in that the GI Genius™ will be turned on and activated for at least the whole of the inspection phase of withdrawal, although the investigators recommend to participating colonoscopists that the GI Genius™ is activated prior to the procedure. Procedural data will be recorded onto a Case Report Form (CRF). Post‐procedure, participants in both arms will undergo standard post‐colonoscopy care and discharge procedures for each site.

Prior to discharge participants will be given a patient experience questionnaire (the validated Newcastle ENDOPREM™ [37]) and a second iteration of the EQ‐5D‐5L to complete and return in a pre‐paid envelope. Follow‐up will cease upon completion of a post‐procedure review between days 14 and 21. This may include accessing medical records (including endoscopy reports and histology) and a telephone call to assess whether any adverse events (AEs) or serious adverse events (SAEs) have occurred. No further contact will be required for study participation, although participants will be asked to consent to long‐term (up to 5 years) passive follow‐up of health outcomes through endoscopy data, medical records and national databases such as the National Cancer Registry Database, Hospital Episode Statistics data, National Endoscopy Database [42] and link to the CORECT‐R data repository [43]. Where data are currently anonymized participant consent will be sought to link data when this becomes possible. Present and future clinical care will be unaffected by study participation.

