Analyses will be performed using a 5% significance level (two‐sided) and effect size estimates will be presented with 95% confidence intervals. All analyses will be completed on an intention‐to‐treat and per protocol basis and will include all randomized patients. We will additionally undertake sensitivity analysis limiting analysis to patients with complete colonoscopy. Should substantial data be found to be missing for a measure or variable (i.e., ≥5%), predictors of missingness will be investigated using regression modelling. Multiple imputation may also be employed to address missing values where appropriate.

A ‘within study’ economic evaluation will be conducted to determine cost effectiveness of GGC versus SC from the perspective of the NHS. It will be based upon the costs of randomized interventions received and on use of subsequent care and services. Use of resources will be collected including duration of procedure, resource use and associated staff costs (including grade of staff), any additional treatment prescribed (e.g., analgesics), appointments missed, any hospital inpatient stays, and any AEs and associated treatment. The EQ‐5D‐5L will provide utility information. Incremental cost effectiveness ratio (cost per quality‐adjusted life‐year) will be estimated with robustness of results evaluated in a sensitivity analysis. The incremental cost effectiveness ratio will be compared against thresholds used to establish value for money in the NHS (currently in the region of £20 000–£30 000 per quality‐adjusted life‐year).

Economic modelling approaches will be used to explore longer‐term economic consequences and patient benefits (including effects on CRC) of GI Genius™, across a lifetime horizon.

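### The NHS cost-per-QALY threshold is attached to the short-term within-study ratio, not to the lifetime model that contains the cancer effects

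*Protocol article*

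**What the plan says.** The economic plan is in the Protocol article, Data analysis. A within-study "economic evaluation will be conducted to determine cost effectiveness of GGC versus SC from the perspective of the NHS". It is based on the randomized interventions and on later use of care and services. The EQ-5D-5L "will provide utility information". In the same paragraph the cost-per-QALY ratio "will be estimated with robustness of results evaluated in a sensitivity analysis", and that ratio is then to be "compared against thresholds used to establish value for money in the NHS", put at £20 000–£30 000 per QALY.

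The next paragraph has a different verb and no threshold: "Economic modelling approaches will be used to explore longer"-term consequences and patient benefits, including effects on colorectal cancer, over a lifetime horizon.

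The timing of the utility data is in Study process. On attendance "consent will be confirmed in writing and participants will complete the" EQ-5D-5L, before randomization. One further EQ-5D-5L is handed out before discharge and returned by post. Follow-up ceases after a post-procedure "review between days 14 and 21". Passive follow-up of records for up to 5 years is by consent and has no utility measure. Data collection adds a written questionnaire reminder at 4 weeks, so some returns may come later than that.

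**The concern.** The trial's reason for seeking more adenomas is that removing them prevents later cancer. The Introduction links detection rate to post-colonoscopy cancer, which it defines over 3 years. The Discussion says that differences in surveillance interval will make a key contribution to the economic evaluation. Both the cancers avoided and the extra surveillance fall after the few weeks in which utility is measured. The effects expected within those weeks, described under Adverse events, are a somewhat longer procedure, possible discomfort and possibly more polypectomy complications.

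So the threshold is applied to the analysis that cannot hold the main benefit or the main downstream cost. The analysis that can hold them has no threshold. Cost effectiveness is a headline aim in the Abstract, and the Discussion says such evaluation should inform commissioning and purchasing. Two results with different horizons, and no statement of which one is judged against the threshold, leave room for conflicting conclusions and for a choice between them after the results are known.

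**Working it through.** **No figure to reproduce.** The economic section gives no computed result, and the article gives no costs, utilities or utility SDs. The arithmetic below therefore only bounds the size. Values marked *assumed* are not in the document.

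**Inputs from the article:** threshold £20 000–£30 000 per QALY (Data analysis); end of active follow-up at days 14–21 (Study process); written reminder at 4 weeks, used here as a 28-day case (Data collection); 2032 participants at 1:1, so 1016 per arm (Sample size).

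**Step 1: the most QALYs available.** Full health for *d* days is *d*/365.25.
- 14 days: 0.0383
- 21 days: 0.0575
- 28 days: 0.0767

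**Step 2: value of a between-arm difference.** QALY difference = utility difference × *d*/365.25. Multiply by £20 000 and £30 000. The utility differences are *assumed* and held constant throughout.

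| Utility difference | 14 days | 21 days | 28 days |
|---|---|---|---|
| 0.005 | £4–6 | £6–9 | £8–12 |
| 0.01 | £8–12 | £12–17 | £15–23 |
| 0.02 | £15–23 | £23–35 | £31–46 |
| 0.05 | £38–57 | £57–86 | £77–115 |

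For 0.01 over 21 days: 0.01 × 0.0575 = 0.000575 QALY; × £20 000 = £11.50; × £30 000 = £17.25. If the difference is instead interpolated linearly from zero at baseline, each value halves. The values scale in proportion to days, so a 42-day horizon only doubles the 21-day column.

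**Step 3: what the ratio then depends on.** The utility gain needed to meet the threshold over 21 days is cost ÷ threshold ÷ 0.0575.
- *Assumed* net cost £10: 0.006–0.009
- *Assumed* net cost £50: 0.029–0.043
- *Assumed* net cost £100: 0.058–0.087

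With a 0.02 gain over 21 days (0.00115 QALY), an assumed cost of £20 gives 20/0.00115 ≈ £17 400 per QALY, and £50 gives 50/0.00115 ≈ £43 500. The result can fall on either side of the threshold according to a few tens of pounds. Prevented cancer plays no part in it.

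**Step 4: precision.** The 95% half-width of the QALY difference over 21 days, without baseline adjustment, is 1.96 × SD × √(2/1016) × 0.0575.
- *Assumed* SD 0.15: 0.00075
- *Assumed* SD 0.25: 0.00125

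An estimated difference of 0.01 (0.000575 QALY) would have an interval that includes zero throughout this SD range. A difference of 0.02 (0.00115 QALY) would have an interval that excludes zero when the SD is below 0.02/(1.96 × √(2/1016)) ≈ 0.23. Baseline adjustment would narrow both intervals.

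**The case against.** The strongest reply is that the lifetime analysis is already planned, in the paragraph right after the threshold sentence, and that nothing forbids applying the threshold to it. The article calls neither analysis the base case, and it condenses a fuller protocol that may settle the matter. Part of this stands: the economic plan as a whole does cover cancer effects. But the threshold's place is stated, not left out. The only ratio and the only threshold comparison are in the within-study paragraph, and the text should not leave the link to be guessed.

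A second reply is that the horizon of days 14–21 is inferred. That is correct: it is the participant follow-up window, no economic horizon is given, and later care and postal returns could extend it. The size barely changes at 28 days, and a later horizon would have no further utility measurements.

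A reader might go further and infer that the within-study ratio must be undefined, dominated or very high whatever the technology's true value, or that more polypectomy can only lower short-term utility. The article supports neither. It gives no costs or utilities, a cost-saving result is possible, and a low assumed cost with a modest gain falls below the threshold, as shown above. Nor would the trial necessarily misreport its objective, since Box 2 words that objective as collecting data for a later economic evaluation.

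**Conclusion.** The concern holds in a limited form. As written, the threshold comparison belongs to a ratio whose QALYs cover a few weeks around the procedure. That ratio excludes later cancers avoided and future surveillance, and at an assumed 0.01 utility difference over 14–28 days its QALY component is worth about £8–23 per patient. Such a comparison is uninformative about value for money and could disagree with the lifetime model.

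That the short-term ratio cannot contain QALYs from prevented cancers follows from the document's own timing of utility measurement. The monetary sizes rest on assumed utility differences, and the ratios and intervals on assumed costs and SDs; they show scale and do not predict the result. A fuller economics plan, not shown, may already name the base case. If so, the article's wording should be brought into line with it. The change is worth making because cost effectiveness is a headline aim and both analyses are already planned.

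**What to change.** Before data are seen:
- Name the lifetime-horizon model as the base case for the £20 000–£30 000 per QALY comparison, with pre-specified sensitivity analysis of its assumptions.
- State the horizon of the within-study evaluation. Report that evaluation as incremental cost per procedure and cost per additional adenoma, or per additional patient with an adenoma.
- Give any within-study QALY result as incremental net monetary benefit, labelled short-term, not as a ratio set against the threshold.

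This is a change of wording and needs no new data or analysis stream. Its cost is that the headline value-for-money result then depends on model assumptions, such as how far extra adenoma removal lowers cancer incidence, so these must be set out and varied openly.
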